**Figure 1 F1:**
[figure not shown]
**Standard Application TheraTogs**.

In the control group cane walking will take place with cane held at the level of the radial styloid of the sound wrist. Occurrences of non-adherence to the protocol will be documented in subject notebooks.

### Measures

Outcome measures will be taken at baseline, defined as the day before intervention begin, the day after intervention is completed (max. 5 weeks), 3 months, 6 months and 2 years after intervention begin.

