**Methods/Design:**

Multi-centre, single blind, randomised trial with 120 patients after first stroke. When subjects have reached Functional Ambulation Category 3 they will be randomly allocated into TheraTogs or cane group. TheraTogs will be applied to support hip extensor and abductor musculature according to a standardised procedure. Cane walking held at the level of the radial styloid of the sound wrist. Subjects will walk throughout the day with only the assigned walking aid. Standard therapy treatments and usual care will remain unchanged and documented. The intervention will continue for five weeks or until patients have reached Functional Ambulation category 5. Outcome measures will be assessed the day before begin of intervention, the day after completion, 3 months, 6 months and 2 years. Primary outcome: Timed "up and go" test, secondary outcomes: peak surface EMG of gluteus maximus and gluteus medius, activation patterns of hemiplegic leg musculature, temporo-spatial gait parameters, hemiplegic hip kinematics in the frontal and sagittal planes, dynamic balance, daily activity measured by accelerometry, Stroke Impact Scale. Significance levels will be 5% with 95% CI's. IntentionToTreat analyses will be performed. Descriptive statistics will be presented.

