### Intervention details

Interventions will be applied for five weeks. If patients become independent walkers before this time (FAC 5) the intervention will be discontinued. If patients are discharged before this time and have not reached FAC 5 where possible the home carer will be instructed in the application of TheraTogs and the intervention will continue for 5 weeks as planned. TheraTogs will be applied as part of the washing/dressing routine in the morning by therapists or nursing staff instructed in the standard application. Subjects will walk throughout the day until preparing for bed with the prescribed walking aid. Standby assistance only will be provided during walking when necessary for safety. No other form of walking aid will be used for the duration of the study intervention. Foot or foot/ankle orthoses will remain unchanged and be worn as usual. All other forms of therapy (frequency and type) will remain unchanged and documented. Patients will receive usual care. When therapists feel that TheraTogs hinders treatment sessions the application may be removed for the duration of the session. It must be immediately reapplied with the standard application following treatment. When necessary TheraTogs may be removed for sleeping in the afternoon. It will be reapplied with the standard application on waking.

TheraTogs is worn directly on the skin. Attached to the basic suit hip abductor support [38] will consist of two broad straps attached 1.to the anterior torso, pulled downwards across the abductors towards and attached to the posterior aspect of the hemiplegic leg and, 2. to the posterior aspect of the torso pulled downwards to cross the abductors and attach to the anterior aspect of the hemiplegic leg. For hip extension one wide strap will be attached to the top of the pelvic rim on the non-hemiplegic side, pulled downwards and laterally passing across the buttock and towards the anterior aspect of the hemiplegic thigh attaching laterally (Figure 1.). Standard application training sessions will be provided to all staff before study begin. Written and photographic instructions will be provided. TheraTogs suits will be marked to ensure consistent application.

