### Sample size and power calculation

In order to detect a clinically significant difference in the primary outcome measure of "Timed up and go" of 10 sec (from a likely range of 10-40 sec), with a probability of 80% at a two sided 5% significance level a total of 116 patients (58 per group) must enter the study. This calculation was performed assuming a SD of the timed up and go of 19 sec [52]. Since there are indications that the distributions of the primary endpoint variable is skewed, the use of a nonparametric test should increase the actual power. To allow for drop-outs 60 participants per intervention will be recruited.

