### Statistical methods

The primary analysis will be performed in an intention-to-treat fashion, i.e. all subjects who where randomised and have at least a Timed Up and Go assessment before start of therapy will be included in all analyses. In the primary analysis, missing values will be replaced by the last available value. If no value under or after treatment is available, the value measured before start of therapy will be used.

The primary analysis will be performed on the Timed Up and Go after 5 weeks of therapy. A nonparametric two sample Wilcoxon-Mann-Whitney test will be performed. Significance levels will be 5%. As robustness analyses, an analysis of covariance will be performed with the value before start of therapy as covariate and centre and therapy as factors. 95% CI's will be calculated based on this analysis. Descriptive statistics for all data will be presented. For continuous data, this will include the change from pre-therapy values. Pre-therapy values will be compared between groups to identify relevant co-variables.

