## Discussion - implications of the hypothesis

Various forms of walking aids are commonly used in post stroke rehabilitation although the long term effects have been sparsely researched. In order to ensure the positive effect of these treatments and to enable evidence based practice, these interventions should be clinically researched.

Early walking is an important aim of stroke rehabilitation for many reasons including the psychological well-being of the patient, to prevent loss of cardiovascular fitness or the development of secondary musculoskeletal problems. This study questions whether canes are the optimal walking aid to enable early independent walking as their use inhibits rather than stimulates activity of the hemiplegic musculature and reduces the use of automatic balance responses contrary to the aims of rehabilitation. A possible alternative to cane use was recently tested by the authors in whom the immediate effects of TheraTogs were to significantly improve hip abductor muscle activity compared to cane walking or walking without walking aids [38].

The rate of recovery of all impairments after stroke is greatest in the first few weeks and slows down after two to three months. Kwakkel et al. discussed an early window during which rehabilitation has the most long term impact [17]. The potential negative or positive effects of walking aids may therefore be particularly significant in this early stage. To our knowledge no studies have investigated this question before. The results of this study may have important clinical significance and could be used in the development of guidelines for gait rehabilitation following stroke.

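### The primary TUG time point is stated in two conflicting ways, and the visit actually scheduled depends on each patient's own recovery

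*Protocol article*

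**What the plan says.** Statistical methods names the primary time point: "The primary analysis will be performed on the Timed Up and Go after 5 weeks of therapy". The test is then specified: "A nonparametric two sample Wilcoxon-Mann-Whitney test will be performed". An analysis of covariance with baseline TUG, centre and therapy is the robustness analysis. For gaps, "In the primary analysis, missing values will be replaced by the last available value".

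Measures lists the visits after baseline: "the day after intervention is completed (max. 5 weeks), 3 months, 6 months and 2 years after intervention begin". The first of these is tied to the end of the intervention, with five weeks only as its upper limit. The other three are tied to intervention begin.

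The end of the intervention is not fixed. Intervention details states: "If patients become independent walkers before this time (FAC 5) the intervention will be discontinued". The abstract agrees: "The intervention will continue for five weeks or until patients have reached Functional Ambulation category 5".

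The Discussion describes the course of recovery: "The rate of recovery of all impairments after stroke is greatest in the first few weeks and slows down after two to three months".

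**The concern.** A patient who reaches FAC 5 in week 2 has the post-treatment TUG in week 2, and the next scheduled one is at 3 months. A slower patient has it at week 5. Only the visit that feeds the primary analysis moves in this way, and what moves it is walking recovery, which is closely related to what the TUG measures.

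By the article's own account these are the weeks in which recovery is steepest, so being measured early means missing real improvement. The authors' hypothesis is that TheraTogs improves gait recovery. If it also brings patients to FAC 5 sooner, more TheraTogs patients are measured early, near a common functional level, and part of the benefit drops out of the primary comparison. A later analysis plan cannot repair this, because a week-5 TUG that was never taken cannot be recovered.

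**Working it through.** **1. Do the passages allow a consistent reading?** Take a patient who stops at FAC 5 in week 2.

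- If the five weeks in Statistical methods is shorthand for the post-treatment visit, the value used is from week 2.
- If it is literal, the patient has no week-5 value, and the last-value rule brings in the same week-2 TUG.

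Both readings put the same recovery-dependent value into the test. Neither the Wilcoxon test nor the analysis of covariance has a term for time of assessment. If a week-5 TUG were in fact taken in everyone, the problem would not arise, but the schedule lists none.

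**2. The plan's own sample size.** Inputs from Sample size and power calculation: difference 10 s, SD 19 s, two-sided 5%, power 80%. The normal approximation gives 57 per arm; the t-test version gives 57.6, so 58 per arm and 116 in total, as stated. Power at 58 per arm is Φ(10 / (19·√(2/58)) − 1.96) = Φ(0.874) = 80.9%.

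**3. Simple attenuation.** Let pT and pC be the shares stopping early in the TheraTogs and cane arms, and g the seconds of improvement an early finisher forgoes, taken as equal in both arms. Then observed difference = 10 − (pT − pC)·g. The article gives neither the shares nor g, so all are assumed.

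| pT / pC | g (s) | Observed difference (s) | Power, 58 per arm |
|---|---|---|---|
| 30% / 30% | 2, 5, 8 | 10 | 80.9% |
| 40% / 20% | 2 | 9.6 | 77.7% |
| 40% / 20% | 5 | 9.0 | 72.3% |
| 40% / 20% | 8 | 8.4 | 66.3% |
| 60% / 20% | 2 | 9.2 | 74.1% |
| 60% / 20% | 5 | 8.0 | 62.1% |
| 60% / 20% | 8 | 6.8 | 48.7% |

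**4. Recovery curves, first model (all assumed).** Baseline TUG lognormal, mean 35 s, SD 19 s; TUG(t) = 9 + (b − 9)·exp(−kt), where b is the patient's baseline; mean k 0.15 per week for cane and 0.25 for TheraTogs, with log-SD 0.5 between patients; FAC 5 represented by a TUG of 14, 18 or 20 s; measurement at the earlier of five weeks and that point. P is the probability that a TheraTogs patient is faster, with ties counted as half. Power with 60 per arm is approximately Φ(|P − 0.5| / √(121/(12·3600)) − 1.96), computed from unrounded P.

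| Measurement | Mean difference (s) | P | Power |
|---|---|---|---|
| Fixed week 5 | 4.3 | 0.64 | about 77% |
| At stop, 14 s | 3.8 | 0.63 | about 72% |
| At stop, 18 s | 3.0 | 0.60 | about 50% |
| At stop, 20 s | 2.6 | 0.59 | about 37% |

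The loss in mean difference is 0.5/4.3 = 12%, 1.3/4.3 = 30% and 1.7/4.3 = 40%.

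**5. Recovery curves, second model (all assumed).** Median baseline 38 s, floor 10 s, TheraTogs recovery rate 2 to 2.5 times that of cane, proxies of 15, 20 and 25 s. TheraTogs patients are measured 0.3 to 1.0 week earlier on average. The mean difference shrinks by 5 to 12%, 20 to 26% and 36 to 40%; one example at 20 s is 9.7 to 7.4 s. It is reduced in every scenario and never removed or reversed.

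**6. Equal recovery.** With the same rates in both arms, measurement times have the same distribution and no bias appears.

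**The case against.** Four arguments stand against the point.

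*The measure is coherent.* The day after completion is a legitimate end-of-treatment assessment, and the abstract and Measures agree on it. That is true, but it conflicts with the five weeks named for the primary analysis, and it still lets measurement time depend on recovery.

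*The sizes come from assumptions.* This stands. No passage maps FAC 5 to a TUG value; the article describes FAC levels by the help needed. The first model also lets some patients start below the assumed threshold (6%, 15% and 20% at 14, 18 and 20 s), so they stop at once with their baseline value. Without them, simulated Wilcoxon power is 82%, 83% and 79% under the written schedule against 86%, 92% and 94% at a fixed week 5, a loss of 4, 9 and 15 points.

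*Later visits are unaffected.* The 3-month, 6-month and 2-year assessments are fixed from intervention begin, so a lasting benefit could still be seen there. They are not the primary analysis.

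*The rank test.* A reader might infer that the Wilcoxon test suffers more than the mean difference because early finishers pile up at one value. The calculation does not support this. Ties receive mid-ranks, and in simulated samples of 60 per arm from the first model the Wilcoxon test has power of 72%, 54% and 41% under the written schedule, against 63%, 52% and 41% for the t-test. The pile-up at a single value is itself a product of using a sharp TUG cut-off for FAC 5.

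**Conclusion.** The contradiction is certain from the text: the primary analysis names a five-week TUG that the schedule does not provide for early finishers, and the value that replaces it is timed by recovery.

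The bias is conditional. It requires the arms to differ in how often or how soon they reach FAC 5, or in the improvement forgone. If TheraTogs speeds recovery, the difference is pulled toward zero; if cane patients reached FAC 5 sooner, the bias could favour TheraTogs.

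A reader might go further and infer that the arms are measured at different times, or that a true benefit is hidden. The article supports neither. It shows only that individual patients are measured at different times, and it gives no FAC 5 rates by arm. The supportable statement is attenuation of unknown size: about 5 to 40% of the mean difference across the assumed curves, with the power losses shown above. Because 60 recruited against 58 required leaves two spare patients per arm, the plan has little room to absorb even a moderate loss.

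**What to change.** Take the primary TUG in every patient at a fixed five weeks after intervention begin, with a short window (for example day 35 ± 3), whenever the intervention stopped. For early finishers, move the existing post-treatment visit to that date. Make the abstract, Measures and Statistical methods name this time point in the same terms. If a TUG on the day after completion is also wanted, label it secondary. The FAC 5 discontinuation rule and the sample size do not change.

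The cost is a small amendment to the assessment schedule. Early finishers, some already discharged, must return at week 5, and keeping both assessments would give them an extra visit. They would also be measured after some time off the device, so the primary result would describe the assigned strategy at five weeks and not the state at end of treatment. The amendment should say so.

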### Baseline descriptives

At baseline descriptive variables for each patient including age, sex area and type of infarct, side of stroke, time since stroke, height and weight will be recorded.

### Primary outcome

The primary outcome measure will be the time taken to complete the Timed "Up and Go" Test [41]. This is a basic test for functional mobility which has good reliability and validity [41,42]. The seat height will be 65% of the subjects leg length and subjects will turn towards the unaffected side [43].

### Secondary outcomes

The following secondary outcomes will be measured during walking and during sit to stand (in "Timed up and go"):

*Peak surface EMG *measurement of gluteus maximus and gluteus medius muscle (TMS International, Enschede, Holland);

*Activation patterns *of gluteus maximus, gluteus medius, vastus lateralis, semitendinosis, gastrocnemius and tibialis anterior;the peak SEMG amplitude of the maximum voluntary contraction of the unaffected gluteus maximus and medius will also be measured.

*Temperospatial gait parameters*--gait speed, cadence, step length, stride length, stance phase and swing phase of both legs; hip kinematics in the frontal and sagittal planes using twin-axis electrogoniometers (Biometrics Ltd UK, USA SG 150).

An intergrated system The Porti-system with a Polybench software package (TMS International, Enschede, Holland) will be used to simultaneously measure these parameters together with a synchronised camcorder with a sagittal view.

*Dynamic balance *will be simultaneously measured using two angular velocity sensors (fibreoptic gyroscopes) of the SwayStar balance system (Balance International Innovations GmbH, Iseltwald, Switzerland) [44,45].

*Muscle strength *of hemiplegic and non-hemiplegic hip abductors will be measured using a hand held dynamometer.

*Daily activity *during the intervention will be measured using an accelerometer (Aipermon GmbH, Germany). Activity modes and accelerometer detection accuracy have been validated [46].

*Social participation *will be measured using The Stroke Impact Scale (SIS) [47]. Validated German, French and Italian versions will be used [47,48]. The Stroke Impact Scale is a stroke specific evaluative instrument that measures the impact of stroke in multiple domains including physical, emotional, memory/thinking, communication and social participation. It is a face-to-face interviewer administered instrument that takes 15 to 20 min to conduct [47].

*"Usual care" *will be documented daily for each patient in a specifically designed questionnaire. Each 10 min treatment block will be classified into 1 of 5 categories. (See attachment "Documentation Standard Therapy.").

Technical details about the measurement of primary and secondary outcome variables are explained below.

### Testing procedure

Physical measurements take place and data collection is performed in a specific, standardised order, conform to the following protocol:

1. Hip abductor muscle strength on both sides of the body will be measured using a hand-held dynamometer. Each test will be performed three times for each leg starting with the healthy leg then alternating. Subjects will rest for 30 sec between trials. Subjects will lie in supine on an examination plinth. Two Velcro straps will be applied to stabilise the pelvis (applied over both anterior superior iliac spines and attached to the bed) and the thorax/spine (applied to the chest below the breasts and attached to the bed). Hips will be positioned in neutral extension and rotation, hip abduction in mid range and knee in extension. The dynamometer will be held perpendicular to the thigh above the lateral femoral condyl of the leg being tested with one foot of the tester against a wall for stability. Subjects will be instructed to push with maximum effort. One practice trial will be carried out prior to testing. A four second hip abduction isometric maximal contraction will be recorded. Mean maximum force over 3 measurements for each leg will be calculated [49].

2. Subjects will rest for five minutes after which a Maximun Voluntary EMG Contraction (MVC) of the non-hemiplegic gluteus maximus and gluteus medius will be measured. The skin will be prepared for surface EMG placement. Skin will be shaved over the appropriate muscles and cleaned with alcohol. Surface EMG electrodes (Kendall, Tyco/Healthcare) will be placed onto the skin overlying these muscles following the "European Recommendations for Surface Electromyography" (SENIAM) guidelines with a spacing of 20 mm [50]. The ground electrode will be placed on the clean shaven skin overlying the sacrum. EMG is measured at a sampling rate of 2048 Hz without filtering so that the signals are measured including DC. The digitalised data will be high pass filtered with a fourth order filter with a cut off frequency of 10 Hz and full wave rectified. To test gluteus maximus subjects will lie prone on an examination plinth. With hip and knee extended manual resistance will be given at the ankle joit in the opposite direction to movement. Subjects will be asked to slowly increase the force, reaching maximum effort after 3-5 sec, hold it for 3 sec and relax over 3 sec. A rest for 1 min will provided after which the test will be carried out once more. The maximum value from both tests will be used a s MVC.

To test gluteus medius, subjects will lie on the hemiplegic side. < the subject will beinstucted to lift leg sideways and manual resistance will be applied at the ankle in the opposite direction to movement. Subjects will be asked to slowly increase the force, reaching maximum effort after 3-5 sec, hold it for 3 sec and relax over 3 sec. A rest for 1 min will provided after which the test will be carried out once more. The maximum value from both tests will be used a s MVC.

3. Electrodes will be removed from the non-hemiplegic side and will be applied with the same procedure as described above to the hemiplegic muscles of gluteus maximus, gluteus medius, vastus lateralis, semitendinosis, gastrocnemius and tibialis anterior. Henna will be applied to ensure accurate replacement at subsequent sessions.

4. The electrogomiometer, foot switches and SwayStar instrumentation will also be fitted. A biaxial electrogoniometer will be placed over the anterior hemiplegic hip joint line, proximal arm in line with the anterior superior iliac spines, distal in line with the axis of the femur. Foot switches will be placed under the calcaneus and the third distal phalange of each foot to measure "initial contact" and "foot off" simultaneously with the EMG. SwayStar will be strapped to the patient's waist.

5. Patients will complete the "Timed up and go test". Time taken will be recorded, EMG activity, dynamic balance and hip kinematics will be collected and video recordings will be taken.

6. Subjects will then rest for five minutes after which they will walk for twelve gait cycles three times. Subjects will rest for five minutes between each set of twelve gait cycles. Data collected during the first two and last two gait cycles will be excluded. Data from the three sets of eight remaining gait cycles will be used to calculate mean values.

7. Patients will rest for ten minutes and then walk over a set of four low (24 cm high) barriers placed 1 m apart.

8. Measurement equipment will be removed, patients will rest for 20 min with a drink after which the SIS will be completed.

### Analysis

Hemiplegic peak EMG values of gluteus maximus and medius will be compared as a percentage of the maximum voluntary contraction peak EMG value of the same muscles of the unaffected leg.

Activation patterns of gluteus maximus, gluteus medius, vastus lateralis, semitendinosis, gastrocnemius and tibialis anterior will be assessed at baseline and at subsequent data collection points. On and off times for each muscle during each stride will be calculated. An amplitude of two standard deviations higher that the resting (reference) amplitude will be considered "on" activity. All detected on- and off- times will be normalised in time using the stride time from the related heel strike measured by a foot switch. SEMG will be rectified and filtered with a high pass fourth order filter with a cut off of 10 Hz and plotted with the timing information along the x-axis. Total burst duration (gait cycle time minus off time) and median on and off times in percentage of the gait cycle will be calculated for each subject for each muscle. Activation patterns will be compared to established normal patterns.

For kinematic measures mean hip range of movement during 1 gait cycle in the frontal plane (ab/aduction) and in the sagittal plane (flex/ext) will be measured for the intervention groups and compared with normal values for matched controls.

Balance control will be assessed with four measurements consisting of trunk pitch (forwards-backwards) angular displacement and velocity and roll (side to side) angular displacement and velocity. Measurements will be taken during all tasks. The fibreoptic gyroscopes (SwayStar) will be attached via a belt to the subjects so that the sensors are at the level L2/3. The sensors will be attached to a computer via a Bluetooth communication, which will sample the velocity signals every 100 ms and numerically integrate the velocity signals to yield angular displacement. The mean will be taken from the maximum values of the two angular displacement measures and the two angular velocities for the cane and TheraTogs intervention groups. The Sway Star has been has been used to assess static and dynamic balance in healthy individuals of differing ages [44,51] and for institutionalised older individuals [45]. The means obtained for the intervention groups post treatment will therefore be compared to baseline values and to established normal values.

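### The protocol gives two opposite orders for filtering and rectifying the EMG, and the order worded for activation patterns would, taken literally, remove the burst envelope

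*Protocol article*

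**What the plan says.** Testing procedure, step 2, describes the recording: "EMG is measured at a sampling rate of 2048 Hz without filtering so that the signals are measured including DC". It continues: "The digitalised data will be high pass filtered with a fourth order filter with a cut off frequency of 10 Hz and full wave rectified". This stands under the maximum voluntary contraction (MVC) of the sound side. Step 3 says that the electrodes "will be applied with the same procedure as described above to the hemiplegic muscles". That phrase concerns electrode placement, and whether it also carries over the signal processing is left open.

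The Analysis section then describes activation patterns. The 'on' rule comes first: "An amplitude of two standard deviations higher that the resting (reference) amplitude will be considered" on activity. After a sentence on normalising to stride time comes the processing sentence: "SEMG will be rectified and filtered with a high pass fourth order filter with a cut off of 10 Hz and plotted" against the timing information. The derived measures are "Total burst duration (gait cycle time minus off time) and median on and off times in percentage of the gait cycle".

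Peak EMG and activation patterns are listed under Secondary outcomes. The primary outcome is the Timed Up and Go time.

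**The concern.** Both sections use a fourth-order 10 Hz high-pass filter and a rectification, but in opposite orders. The order matters. A muscle burst appears as a slow rise and fall in the rectified signal, mostly below about 10 Hz. High-pass filtering before rectifying removes offset and drift and leaves that profile intact. High-pass filtering after rectifying removes the profile itself and leaves a residual that fluctuates around zero.

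The DC component adds a second problem. If the raw signal is rectified first, the outcome depends on how large the electrode offset is relative to the EMG. When the offset exceeds the EMG amplitude, rectification changes nothing and the high-pass filter returns ordinary bipolar EMG. Offset is a nuisance of electrode contact, and the measurements are repeated at five time points.

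The activation patterns bear on the trial's stated mechanism, that the cane inhibits and the orthosis increases hemiplegic muscle activity. The Analysis section also compares them with established normal patterns, which requires one defined and valid processing sequence.

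**Working it through.** The document gives no figure on this point, so there is none to reproduce. The check is a simulation.

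**Inputs from the document:** sampling at 2048 Hz with DC included; fourth-order high-pass at 10 Hz; 'on' threshold two SDs above rest.

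**Assumptions not in the document:** Gaussian EMG limited to 20-450 Hz, a 1.4 s stride, Butterworth filters, burst-to-rest amplitude ratios of 3, 5 and 10, and a threshold applied sample by sample.

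**1. Amplitude, abrupt burst filling 40% of the cycle, no offset.** Mean in-burst amplitude at ratios 3, 5 and 10:
- high-pass, then rectify: 2.40, 4.00, 8.00
- rectify, then high-pass: 0.03, 0.06, 0.14
- quotients: 0.03/2.40 = 1.3%, 0.06/4.00 = 1.5%, 0.14/8.00 = 1.8%

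**2. 'On' time for the same burst.** Rectify, then high-pass gives 12%, 15% and 18% of the cycle. At ratio 5, an offset of three resting SDs moves 15% to 12%. With an offset the low end of the range is about 10%.

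**3. Second run, with 3% ramps at each end of the burst.** Active time between the ramp midpoints is 37.0% of the cycle. Each cell gives 'on' time as a percentage of the cycle, then switches per stride.

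| Ratio | High-pass, rectify | Rectify, high-pass, offset 3 SD | Rectify, high-pass, no offset | High-pass, rectify, 10 Hz low-pass | High-pass, rectify, 25 Hz low-pass |
|---|---|---|---|---|---|
| 3 | 22.2; 500.5 | 9.1; 239.5 | 11.6; 353.1 | 41.4; 3.3 | 40.0; 5.8 |
| 5 | 28.7; 495.4 | 11.1; 287.5 | 14.1; 399.6 | 42.5; 3.5 | 40.7; 5.6 |
| 10 | 34.9; 386.0 | 13.6; 351.1 | 16.5; 443.4 | 43.6; 4.0 | 41.6; 5.8 |

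Mean amplitude in and out of the burst is 2.48/0.81, 3.99/0.82 and 7.82/0.86 for high-pass then rectify. It is 0.00/-0.00, 0.01/-0.01 and 0.04/-0.02 for rectify then high-pass with the offset. Under the literal Analysis order, burst duration is understated by between (37.0 - 16.5)/37.0 = 55% and (37.0 - 9.1)/37.0 = 75%.

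**4. Why reversing the order is not enough by itself.** For rectified Gaussian noise with SD 1, the mean is 0.798 and the SD 0.603, so the threshold is 0.798 + 2 × 0.603 = 2.004. At rest, P(|Z| > 2.004) = 4.5%. In a burst of ratio k, the share of samples above threshold is P(|Z| > 2.004/k): 50.4%, 68.9% and 84.1% for k = 3, 5 and 10. With a 40% burst, 'on' time is then:
- 0.4 × 50.4 + 0.6 × 4.5 = 22.9%
- 0.4 × 68.9 + 0.6 × 4.5 = 30.3%
- 0.4 × 84.1 + 0.6 × 4.5 = 36.3%

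This agrees with the simulated 23%, 30% and 37%. Rectified EMG falls to zero at every zero crossing, so single samples keep dropping below threshold inside the burst. That is the source of the hundreds of switches in the table.

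**5. Cost of smoothing.** A 6 Hz envelope brings switches down to about 2-4 per stride but widens a 40% burst to 46-50%. The 10 and 25 Hz envelopes in step 3 widen 37.0% to 40.0-43.6%, part of which is the ramps and occasional false detections at rest.

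**The case against.** The strongest reply is that the processing sentence in the Analysis section concerns plotting. The 2-SD rule stands earlier in the paragraph as a separate sentence. Nothing says that it uses the rectified and then filtered trace, or that it works sample by sample. This stands. A reader might infer that on/off times and burst duration will be wrong; the text supports only that they would be if the rule is applied to that trace. The 'on' shares and switch counts are conditional in the same way.

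Rectified and filtered may also be a loose list rather than a sequence, so that one pipeline is described twice. That is possible. But the two sentences contradict each other as worded, and even as a display step the literal order yields a plot without the burst profile.

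A condensed article may leave smoothing windows and minimum durations to the full protocol. This also stands: their absence is not an error here. Smoothing enters only because putting the order right would not give usable on/off times under a sample-wise threshold.

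Finally, a reader might infer that peak EMG as a percentage of MVC is spoiled as well. That is not shown. It does not depend on the plotting sentence, the Testing procedure order keeps the amplitude contrast, and no effect on the peak was quantified.

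**Conclusion.** The point holds in a limited form. The two sections contradict each other on a processing step that is stated, not merely omitted. The order worded for activation patterns, followed literally, reduces mean in-burst amplitude to about 1-2% of that under the other order (lower still with ramped bursts) and makes the result depend on electrode offset. The plotted patterns would be wrong. On/off times and burst duration would be wrong only if the 2-SD rule uses that trace; with an assumed sample-by-sample rule, 'on' time would be about 10-18% of the cycle against a true 40%.

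The loss of the envelope follows from the order of the steps. The exact percentages rest on the assumed signal, stride time, burst ratios and offset. Fast fluctuation within the burst remains larger than at rest, so bursts would still be visible, but without their profile. The primary outcome, its analysis and the sample size are untouched.

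**What to change.** State one order in both the Testing procedure and the Analysis section: high-pass filter the raw signal at 10 Hz, then full-wave rectify. Name the signal that the 2-SD rule uses, preferably a smoothed envelope (low-pass or RMS window) of that rectified signal, with the resting mean and SD taken from the same envelope. Use the same pipeline for the gait recordings and the MVC, so that the peak ratio compares like with like.

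The cost is a change of wording and a little processing code. Signals are recorded unfiltered, so no new data collection is needed. The one drawback is that smoothing widens bursts somewhat (a true 40% becomes about 45-50% in simulation, depending on the cut-off), so the cut-off or window must be fixed before the data are analysed.
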